**(3) Advances scientific theory on multi-level HIV status-neutral interventions** by testing an *OFOV* model that specifies how a behavioral risk-reduction framework *and* an asset-based framework model interact together to produce synergistic effects. It is further innovative for its focus on families rather than singling out sub-groups of family members based on HIV status. Implementation-related advances include that PLHIV may benefit from not having to not openly disclose their HIV status to participate in an intervention with other members of their community. The family gets the same information for HIV treatment and HIV prevention (e.g., PrEP, U=U) that becomes a communal exchange of knowledge within the family that has the potential to shift family norms, transform perceptions and minimize stigma. Status-neutral strategies represents a next generation response to the epidemic by dismantling HIV stigma that is embedded in the structure of interventions.

- 1. **APPROACH**

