**3.4.1 Study Design Overview.** We will determine the feasibility, acceptability and a preliminary estimate of effect size of an evidence-based HIV prevention intervention for Black MSM adapted for HIV status-neutral use with families in the HBC (called: *OFOV*). The eight-step ADAPT-ITT framework^17,18^ will guide our approach to enhancing the intervention’s content to incorporate an asset-building framework that leverages the strengths of the families. Aim 1 will encompass steps 1-7, leading to the combined multi-level intervention adapted to improve congruence with the realities of HBC family life. Aim 2 encompasses step 8, in which we will assess the feasibility and acceptability of conducting a cluster randomized controlled trial (CRCT) of *OFOV* with a standard of care wait-listed control condition (see section 3.6.1). We will use data collected from the CRCT to estimate the effect size of *OFOV* on **HIV testing and PrEP use** (primary outcome for HIV-negative participants), **HIV care engagement** and **currently on ARV treatment** (primary outcome for PLHIV), as well as **number o**f **family-based assets** and **number of sex partners** and **relative** **frequency of CAI** (status-neutral secondary outcomes). In deciding on the wait-listed controlled CRCT we considered other designs such as factorial designs and a classic RCT design with time and attention-matched controls. We do not yet seek to isolate which component of the intervention has the greatest effect on our outcomes; thus, a factorial design was not scientifically justified for our proposed study. Additionally, we decided to forgo a structurally equivalent control group given the evidence of 3MV’s efficacy in risk reduction and increasing HIV testing.

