Our working hypotheses are that the *OFOV* intervention will increase uptake of HIV testing and PrEP use (for HIV-negative family members) and linkage to care and treatment engagement (for PLHIV who were not in care at baseline). We will measure frequency of HIV testing at 3- and 6-months post-intervention using a combination of online self-report survey and verification by through clinic medical records. We will seek to obtain medical records releases from participants to obtain data on HIV testing, PrEP prescription, engagement in care and ARV use. Our secondary hypotheses are that *OFOV* will increase the number of family-based assets, resilience and reduce number of sex partners and frequency of CAI for members who are not in mutually monogamous relationship with an HIV-negative or virally suppressed partner. We also measure intersectional stigma and asset-impact indicators at all time points (to characterize these in our sample) ^102,103^ Families in the waitlist SOC control arm have the option to participate in OFOV after 6-month data collection.

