**3.6.4 Data Collection and Measures.**

**3.6.4A Data collection.** Participants will have the option of either receiving an electronic link to complete baseline, 3- and 6-month surveys or they can visit the HEAT clinic and complete the online survey using internet-enabled computer tablets. Survey data will be collected using research and data capture (ReDCap) software. All trial participants will receive the same surveys, with the exception that only the intervention arm will be assessed on implementation process measures (Tables 4). Participants will be given gift card incentives after the survey completion at baseline, 3 and 6 months for a card value of $50, $75 and $75, at those respective time points.

We will also collect data via medical record review. All participants will be asked to complete a medical record release authorization form that will allow us to request the following information from their medical provider(s): HIV testing in past 3 months, last prescription written for HIV PrEP or last ARV prescription written for treatment and last PrEP or HIV medical appointment kept.

**3.6.4B Demographic, Knowledge and Behavioral Factors**. We will assess important baseline characteristics for describing the sample including age, income, gender, education, ethnicity, relationship status, religion, sexual identity, sexual behavior, HIV knowledge, HIV testing readiness, HIV testing history. We will characterize the sample on intersectional stigma by creating a latent variable that is drawn from three scales that measures HIV stigma, same-sex stigma, and gender non-conforming stigma (see Table 4).

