**3.6.4C Primary and Secondary Outcomes.** Our primary outcomes will be HIV testing and PrEP use (for HIV-negative or unknown members) or “In HIV care” and “currently on HIV treatment” (for PLHIV) within 6 months of randomization. For HIV-negative MSM we will also record the frequency of HIV testing over the prior 3-months, but we anticipate that few participants will take >1 test in this short period of time. A detailed summary of primary outcome measures is included in Table 3. Our secondary outcomes (see also Table 4) will be number of family-based assets, resilience, number of sexual partners, and relative frequency of CAI. We will also assess sense of community^105^ at all time-points. In our previous research with Black MSM we found that sense of community was associated with increased condom use for anal intercourse (*OR*=1.26, 95%CI 1.05,1.52; p<.05).^14^

**3.6.4D Implementation Outcomes.** We will assess feasibility and acceptability of *OFOV* using a combination of process measures (e.g., intervention completion rate) and validated scales (e.g., peer support evaluation inventory). Implementation outcomes measures are also summarized in Table 4.

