The likelihood of intervention contamination across the study groups could not be excluded, because some participants may not receive the respective interventions to which they are randomized, e.g., some members of the control group may end up in situations in which they receive some level of support from a HBC family in the intervention group. Therefore, we will also perform per-protocol analysis, which includes only those participants who strictly adhered to the protocol and report the results along with the results of the ITT analyses.

| **Table 4. Summary of RCT Phase Measures** | |
| --- | --- |
| **Construct** | **Sample Items and reliability** |
| **HIV Testing** (self-report and medical record verified) | Number of HIV tests in past 3-months |
| **PrEP Use** (self-report and medical record verified) | Is participant currently on antiretrovirals for HIV PrEP? |
| **In HIV Care** (self-report and medical record verified) | Has participant attended HIV medical appointment in past 3-months |
| **On HIV Treatment** (self-report and medical record) | Is participant currently on antiretrovirals for HIV treatment? |
| **Condomless anal intercourse** (past 3 months) | Relative frequency = # times condoms used during anal sex / total # episodes of anal sex |
| **Number of sexual partners** | Total number of sexual partners in the past 3 months |
| **Sense of Community Scale^105^** (8-items) | I feel like I am a member of my house family (α=0.87 - 0.92) |
| **Brief Resilience Scale^106^** (6-items) | I tend to bounce back quickly after hard times? (α=0.80-0.91) |
| **READY Tool** (24-items)^102,103^ | My family expects me to try my best. I ask my family questions to get ideas. (α=0.85) |
| **Asset Inventory (40-items)^21^** | I seek advice and counsel from my parents. My family has clear rules and consequences. |
| **Intersectional Stigma (Latent Variable)** |  |
| **HIV Stigma Scale^107^** | |
| *Enacted subscale (10-items)* | Has a healthcare worker not wanted to touch you because you have HIV? (α=0.92) |
| *Vicarious subscale (10-items)* | How often have you heard stories about someone with HIV being refused care? (α=0.88) |
| *Perceived subscale (10-items)* | In your community, how many people think a person with HIV is disgusting? (α=0.94) |
| *Internalized subscale (10-items)* | How often do you feel guilty about having HIV? (α=0.83) |

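### The hypothesis on partner number and CAI is limited to a subgroup that the outcome definitions do not carry and the listed measures cannot identify; Table 4 also defines CAI as condom use

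*Protocol*

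**What the plan says.** Protocol section 3.6.1 gives the secondary hypotheses. Among them, the intervention (OFOV) is expected to "reduce number of sex partners and frequency of CAI", and the sentence ends with a restriction: "for members who are not in mutually monogamous relationship with an HIV-negative or virally suppressed partner". The grammar leaves open whether the restriction covers partner number as well as CAI.

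The places that define the outcomes carry no restriction:

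- Section 3.4.1 groups number of assets, number of partners and relative frequency of CAI as "status-neutral secondary outcomes".
- Section 3.6.4C says: "Our secondary outcomes (see also Table 4) will be number of family-based assets, resilience, number of sexual partners, and relative frequency of CAI".
- Table 4 counts all sexual partners in the past 3 months. On the line labelled condomless anal intercourse it gives: "Relative frequency = # times condoms used during anal sex / total # episodes of anal sex".

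For the variables that could define the group, section 3.6.4B lists baseline characteristics that include "relationship status, religion, sexual identity, sexual behavior, HIV knowledge, HIV testing readiness, HIV testing history". Neither that list nor Table 4 names mutual monogamy, the partner's HIV status or the partner's viral suppression. Section 3.6.4A gives all participants the same surveys apart from process measures. Section 3.6.5 states a general intention-to-treat rule and nothing specific to these outcomes.

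**The concern.** The hypothesis and the outcomes describe different populations. A reader cannot tell whether the effect on CAI and partner number is to be estimated in everyone or only in members outside a protected monogamous pair. If it is estimated in everyone, members whom the hypothesis deliberately sets aside dilute the effect. If it is estimated in the subgroup, the protocol lists no data from which to build it.

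Timing is a second issue. Session 5 in Table 3 covers relationships, including how partners are chosen. If the subgroup were formed from follow-up answers, the intervention itself could change who belongs to it, and the randomised comparison would be lost.

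At stake is the effect size on these outcomes, which section 3.4.1 names as something the trial will estimate and which would inform the full trial described in section 3.7.

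**Working it through.** The document shown attaches no sample size, power or event rate to CAI or partner number, so there is no planned figure to reproduce. The check compares the sections and then sizes the dilution on stated assumptions.

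**1. Can the group be formed?** The restriction needs three facts about each member:

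| Fact needed | Listed in 3.6.4B or Table 4? |
|---|---|
| In a relationship | Yes (relationship status, baseline) |
| Relationship mutually monogamous | No |
| Partner HIV-negative or virally suppressed | No |

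One of three is listed. The HIV care and treatment items in Table 4 concern the participant, not the partner.

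**2. Size of the dilution.** Let d be the effect in the hypothesised group, m the share of members outside it, and assume no effect in that share.

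All-member effect = (1 − m) × d + m × 0 = (1 − m) × d

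The protocol gives neither m nor d. The illustration takes d = 15 percentage points and a range for m, both assumptions. The planned sample is 100 (section 3.6.2A).

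| m | Share of effect kept | All-member effect if d = 15 | Members in the group, of 100 |
|---|---|---|---|
| 10% | 0.90 | 13.5 points | 90 |
| 25% | 0.75 | 11.25 points | 75 |
| 40% | 0.60 | 9.0 points | 60 |
| 50% | 0.50 | 7.5 points | 50 |

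The share kept does not depend on d.

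**3. Does restricting cost more than it gains?** With equal spread in both groups and clustering ignored, an all-member analysis needs 1/(1 − m)² times as many members as an undiluted one. A restricted analysis needs 1/(1 − m) times the enrolment to keep the same number analysed. At m = 25% these are 1/0.75² = 1.78 and 1/0.75 = 1.33. On these assumptions the smaller group is not the less informative choice.

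**4. Direction of the Table 4 ratio.** The numerator is episodes with a condom and the denominator is all episodes, so the printed ratio equals 1 − CAI share. If the condomless share fell from 60% to 45% (an illustration), the printed value would rise from 40% to 55%. On a line labelled CAI, with a hypothesis of reduction, the hoped-for change would read as a worsening.

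**The case against.** The strongest defence is that the unrestricted places are only lists of outcomes and measures. None says that CAI is analysed in all members, and the analysis set for a secondary outcome may properly be left to a statistical analysis plan, which is not shown. The list in 3.6.4B is introduced as non-exhaustive, Table 4 presents its entries as sample items, and the survey itself is not at hand. Much of this stands: analysis in everyone is an inference from the absence of a limit, and the survey may contain the missing items. What remains is that the variables defining a stated hypothesis population should be named in the protocol, because a later plan can choose an analysis set but cannot supply answers that were not collected.

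A reader might also infer something stronger: that starting PrEP, a primary success, would lower condom use and so register as harm on CAI. Section 3.3 supports the premise that PrEP and U=U are taught ("The family gets the same information for HIV treatment and HIV prevention (e.g., PrEP, U=U"), and the restriction in 3.6.1 makes no allowance for the participant's own PrEP. The documents do not support the conclusion, for these reasons:

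- It needs lower condom use on PrEP than off it, and the protocol gives no rate for this.
- Under assumed rates the result is still a reduction. Suppose CAI in the group falls from 60% to 45%, except that 20% start PrEP and sit at 80%. Then 0.8 × 45 + 0.2 × 80 = 52%, a change of −8 points, or 0.75 × (−8) = −6 points over all members at m = 25%. Reversal within the group needs more than 15/35 = 43% of members starting PrEP at 80% CAI.
- With the ratio as printed, a switch from condoms to PrEP would score as a reduction.
- Partner number has no condom or PrEP element.
- For antiretroviral treatment, the pilot in 3.4.4C reports increased uptake together with increased condom use.

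Nor should total CAI be replaced by CAI outside PrEP or ARV cover. Scored over all members, that measure falls whenever PrEP use rises, even with unchanged behaviour off PrEP, so it repeats the primary outcome. Restricted to uncovered members, it conditions on a post-randomisation variable. It would also pair current PrEP use with a 3-month recall of acts, and it would set aside the STD content of the curriculum, for which condomless sex matters whatever the PrEP status.

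**Conclusion.** The point holds as a mismatch of populations together with a gap in the listed measures. Section 3.6.1 limits the hypothesis, sections 3.4.1 and 3.6.4C and Table 4 do not repeat the limit, and the group cannot be identified from the listed items. If everyone is analysed, the target effect is kept only to (1 − m), which is 90% to 50% for m from 10% to 50%. This rests on an assumed m and on no effect in the excluded share. The reversed ratio in Table 4 is a separate definitional error and needs no assumption.

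The weight is moderate. These are secondary outcomes of a six-family pilot and no primary conclusion depends on them, but the data gap cannot be repaired once baseline surveys are complete.

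**What to change.** Before baseline surveys are fielded:

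1. In 3.6.4B, add two or three baseline items on mutual monogamy and on the partner's HIV status and viral suppression. Say how unknown partner status is classified.
2. Define the 3.6.1 population from baseline answers only, and state whether it applies to partner number as well as CAI.
3. State that population in 3.6.4C and Table 4, make 3.4.1 consistent with it, and report all-member results alongside.
4. Correct the Table 4 ratio to condomless episodes divided by total episodes.
5. Keep total CAI as the secondary outcome. At most, describe CAI by current PrEP or ARV use next to it, without claiming that PrEP uptake reverses the effect.

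The cost is a few survey items and a smaller hypothesis population. Partner status will be known only as the participant reports it.

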**3.6.2 Procedures**

**3.6.2A Recruitment and Sample****.** We will recruit six HBC families (n=100). See Human Subjects section *4.4. Statistical Design and Power* for sample size and power calculations. We will conduct recruitment using three methods. First, we will disseminate recruitment/marketing materials via **The Federation**, **HLM** and **The Coalition’s** online communication platforms. Potential participating families can contact the study office directly via text message or phone call in response to marketing materials. Second, we will recruit through receipt of referrals of interested families from **The Federation**, **HLM** and **The Coalition’s** programs and outreach activities. Research staff have extensive experience engaging MSM for research and program activities. Third, we will also rely on word-of-mouth as a mechanism through which families become aware of the study and contact us.

**3.6.2B Inclusion/Exclusion Criteria.** Eligibility for the study will be determined primarily at the family-level. At least 12 members of the same HBC family must be willing to participate together, of which at least half the participating members must be Black MSM. Participating family members must reside in the New York City metro area. Black MSM participants must be at least 18 years old. [name], who is a pediatric HIV specialist, believes that the social risk of a confidentiality breach to the biological family is heightened for youth under the legal age of emancipation. Furthermore, we could not justify the risk of enrolling people younger than 18 since our research aim can reasonably be addressed without their inclusion. In addition, Black MSM must also currently self-identify as cisgender or transgender man, report anal sex with another man at least once within the previous six months (note: other HBC family members can identify as any gender).

**3.6.2C Informed Consent.** We will obtain informed consent for each individual family-member prior to study enrollment. HEAT project staff will be responsible for obtaining and ensuring informed consent and will fully explain the study to potential participants and answer all questions regarding what study participation entails. We will ensure that all participants know that their participation is completely voluntary and that they can withdraw at any time, without repercussion. After consenting, participants be given a link to electronically complete the baseline survey on their smartphone, tablet, or desktop computer. Informed consent will be documented by electronic signature on touchscreen computer tablet and stored in research and data capture (REDCap) system. Prior to departure on the retreat, participants will also be asked again to confirm that they still wish to participate.

**3.6.2D Enrollment and Randomization.** Consented individuals will be enrolled in the study consecutively. Given the relatively small number of facilities per arm (N = 3), a covariate-constrained optimization technique (e.g., matching) will be used to randomize intervention assignment and minimize imbalance in the two arms.^104^ This randomization method will be examined in this pilot for consideration of using in future full RCT.

**3.6.3 OFOV Intervention Implementation**

**3.6.3A Retreat Procedures**. Families who are assigned to the intervention arm will be given dates for the weekend *OFOV* retreats they would attend at temporarily rented facilities. Prior to attending *OFOV*, participants will attend an orientation meeting at HEAT to obtain information about the logistics and format of the retreat and to establish ground rules for appropriate behavior. Once participants arrive at the retreat, the *OFOV* intervention will be delivered in six consecutive 2- to 3-hour sessions. The original 3MV sessions content is summarized below (see Table 3). HIV Counseling & Testing staff from HEAT will participate as guest facilitators in one of the *OFOV* sessions and will use that opportunity to reach out to family members to visit their facility for HIV testing, PrEP, engagement in care or HIV treatment.

**3.6.3B Video Boosters.** Four self-contained, video booster session modules will be delivered every 6 weeks post *OFOV* intervention (approximately two boosters between 3 and 6 months). The video boosters are designed to be watched together as a family. The videos will include guided-reflection questions for the family members to discuss. The content of the video boosters will be developed in the formative phase **(see Section 3.5.4).** Based on **[name]** previous work, potential topics of videos range from dealing with HIV status or STI disclosure, importance of consistently taking ARVs, and effective advocacy for family members’ health needs in healthcare settings. The videos will only be available to study participants via a secure URL and will not be able to be forwarded to friends or other participants (preventing cross contamination between arms). Each individual will receive the link to the video and may watch the video before or after the family convenes their group session.

**Table 3. Summary of Original 3MV Intervention, Sessions Topics and Length**

| **Intervention** | **Level** | **Modality** | **Sessions** | **Length (Mins)** |
| --- | --- | --- | --- | --- |
| Many Men, Many Voices /3MV adaptation for HBC-***Our Family Our Voices*** | Peer-Group and Family | Group Sessions using:  *Brainstorms*  *Role Play*  *Small group*  *activity*  *Paired work*  *Develop menu*  *of prevention*  *options*  *Action planning* | 1. MSM and dual identity | 140 |
|  |  |  | 2. HIV/STD prevention for MSM: the roles and risks for tops and bottoms | 210 |
|  |  |  | 3. HIV/STD risk assessment and prevention options | 110 |
|  |  |  | 4. Intentions to act and capacity for change | 170 |
|  |  |  | 5. Relationship issues: Partner selection, communication, and negotiation of roles | 140 |
|  |  |  | 6. Social support and problem solving to maintain change | 125 |
|  |  |  | 7. Building bridges and community | 130 |

**3.6.3C Selection and Training of Interventionists.** Each *OFOV* intervention retreat will be conducted by two facilitators from the HBC. We will identify and train 6 (4 primary and 2 back-up) intervention facilitators from the group of HBC members who have previously attended 3MV retreats. This pool will already have had the experience of undergoing the original intervention and will therefore be more sensitized to the topics and the potential anxieties and wariness of the intervention participants. The facilitators will first receive a two-day training on group facilitation skills in which they will increase their knowledge, confidence and fluidity in group facilitation. They will then be trained on *OFOV* as well as on current state of the science topics, such as U=U.

